## Abstract

**Background:**

Hypertension is a significant risk factor for cardiovascular disease, contributing to global mortality and disability. Approximately 30% of Indian adults are diagnosed with hypertension. Evidence supports that self-monitoring and blood pressure self-management can lower systolic BP by an average of 3.2 mmHg. mHealth applications facilitate remote monitoring and self-management, yet existing applications in India lack customisation for user needs, limiting their usability. This study aims to develop and evaluate a novel, user-friendly mHealth application tailored to hypertensive individuals.

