Where n = number of subjects per arm, δ = effect size, σ = standard deviation, m = cluster size, ρ = intraclass correlation coefficient.

Based on systematic review evidence demonstrating that comprehensive mHealth interventions (combining self-monitoring, medication reminders, and lifestyle support) achieve systolic BP reductions of 4-6 mmHg compared to usual care (
Mekonnen et al., 2022;
Chandrasekhar et al., 2021), we anticipate a conservative effect size of 5 mmHg reduction in systolic BP. Assuming a baseline systolic BP of 145 ± 15 mmHg in our population (
Kumar et al., 2020), a five mmHg reduction represents a clinically meaningful 3.4% decrease. With 90% power, 5% significance level (two-sided), design effect of 1.45 (ICC = 0.05), and accounting for 15% attrition, the required sample size is 118 participants per arm distributed across 12 clusters of approximately 20 participants each (total n = 236). A sensitivity analysis confirms adequate power (>80%) to detect systolic BP reductions as small as 3.5 mmHg, ensuring the study can identify clinically meaningful effects consistent with published mHealth intervention studies.

Randomization will be carried out at the cluster level i.e. the villages would be the units of randomization. The entire process of randomization will be carried out by non-participating biostatistics faculty. Sequence generation will be done according to the block technique, with a block size of 4 for 2 allocation categories: ‘A’ for the new intervention and ‘B’ for the standard intervention, yielding 6 different combinations or sequences. Allocation concealment will be achieved through coded opaque sealed envelopes. Thereafter, the interventions will be allocated to the recruited clusters by the investigators strictly according to the sequence of the block. Each of the 3 steps of randomization, namely, sequence generation, allocation concealment, and implementation will be carried out by an independent faculty.

For the participants in the intervention group, the mHealth application will be installed on their smartphones, and the required data will be entered by the primary investigator. A demo of the application features will be provided. Participants from the intervention group will also be given automated BP apparatus. Under established clinical guidelines, participants will receive comprehensive blood pressure measurement training (
Williams et al., 2018;

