Whelton et al., 2018). The orientation protocol will include: (1) timing specifications requiring BP measurement twice daily (morning: 6-10 AM, evening: 6-10 PM) with at least 12 hours between readings; (2) standardised measurement technique involving three consecutive readings taken 1-2 minutes apart, with the first reading discarded and the mean of the second and third readings recorded; (3) pre-measurement requirements including 5 minutes of quiet rest, avoiding caffeine/exercise 30 minutes prior, proper cuff placement directly on skin (not over clothing), and maintaining feet flat on floor with back supported; (4) technical specifications ensuring appropriate cuff size selection and proper arm positioning at heart level; and (5) data entry protocols for recording measurements in the mHealth application immediately after each session. Participants will demonstrate competency in the BP measurement technique before the study commences, with refresher training provided at monthly follow-up contacts. The control group will receive standard care which includes advice to adhere to their prescribed medication and lead an active lifestyle. Baseline measurements like blood pressure, knowledge and practice of management of blood pressure, self-efficacy, and health status will be obtained from the recruited participants in both groups. Blood pressure will be measured with an electronic BP apparatus ([name] BP monitor-118), which will be calibrated periodically. Knowledge and practice will be assessed using a hypertension fact questionnaire. Self-efficacy using Medication Adherence Self-Efficacy Scale (MASES) and Self-Efficacy for Managing Chronic Disease 6-item Scale will be assessed and health status using SF-36 questionnaire will be assessed for pre and post-test (
Fernandez et al., 2008;
Lorig et al., 2001;
Ware & Gandek, 1998). For any reason, if the participant is unable to use the application, we will be discontinuing the intervention regimen for that participant. Regular phone calls will be made to remind them to use the application and to track their BP. The participants will be allowed to withdraw from the study at any given time as per their decision. The consort flowchart of the phase 3 is shown in
Figure 4.

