## Conclusion

Using mHealth applications for remote monitoring and self-management helps reduce the burden on health-service system. In the proposed research, we will be developing an mHealth application for people with hypertension to meet the local health information needs, provide information in regional language and will be designed based on patient usability feedback. The application will monitor blood pressure, physical activities, medication, diet, and provide recent updates on hypertension management. This application, if found effective, can improve the health status, knowledge, and self-care approach among hypertensive patients by installing the mHealth application. Additionally, it may even minimize the problems caused for accessing healthcare due to the recent pandemic and can be the solution to evade in-person sessions.

Future research should validate this intervention across multiple Indian states, incorporating diverse languages, cultural practices, and healthcare infrastructure variations to establish broader generalizability across India’s heterogeneous population. A multi-state consortium approach could facilitate the development of a scalable mHealth platform with modular language and cultural components, ultimately contributing to nationwide hypertension management improvement. Economic evaluation studies across different socioeconomic contexts would also further inform policy decisions regarding mHealth implementation at scale.

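### The trial compares an app-based package with standard care, but its objective and conclusion are worded as the effect of the application, which two arms cannot isolate

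*Protocol article*

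**What the plan says.** All references are to the protocol article.

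**What the arms receive (Methods, Phase 3).** The investigator installs and demonstrates the application for the intervention group. In addition, "Participants from the intervention group will also be given automated BP apparatus". The same passage goes on to say that "participants will receive comprehensive blood pressure measurement training", which covers "data entry protocols for recording measurements in the mHealth application immediately after each session", "with refresher training provided at monthly follow-up contacts". Later it adds: "Regular phone calls will be made to remind them to use the application and to track their BP". For the comparator: "The control group will receive standard care which includes advice to adhere to their prescribed medication and lead an active lifestyle".

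**What is to be concluded.** The title and the Abstract (Methods) present the trial as a test of the application, and the Abstract describes the arms as app use versus the usual regimen. The Abstract (Results) says patients could be encouraged to use the application if it helps. The Conclusion says that the application, if effective, "can improve the health status, knowledge, and self-care approach among hypertensive patients by installing the mHealth application".

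**What the document says about self-monitoring.** The Introduction gives a 2 to 8 mmHg systolic reduction from self-monitoring. The Abstract (Background) says: "Evidence supports that self-monitoring and blood pressure self-management can lower systolic BP by an average of 3.2 mmHg". The sample size section plans for 5 mmHg, taken from a 4 to 6 mmHg range for multi-component mHealth programmes that include self-monitoring, compared with usual care.

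**The concern.** The stated question is about an application. The contrast tested is about an application delivered with a device, training and repeated staff contact. A reader of a positive result, guided by the Conclusion, would credit the software and could expect the same benefit from installing it. Installation alone brings no monitor, no supervised training and no calls. The section on strengths and limitations discusses smartphone selection, adherence, language and generalisability, but not these accompanying components. So nothing in the article warns the reader that the effect estimated is not that of the application alone.

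**Working it through.** **Step 1. Set the arms side by side.**

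| Element | Intervention | Control | Basis |
|---|---|---|---|
| Application with alert system | yes | no | Phase 2, emergency alert text; Phase 3 |
| Automated BP monitor | yes | not stated in Phase 3 | Phase 3, explicit |
| Measurement training, monthly refreshers | yes | none described | inferred: it follows directly on the intervention text and includes data entry in the application |
| Reminder calls | yes | none described | inferred: the calls concern use of the application |
| Standard care with advice | not described separately | yes | Phase 3, explicit |

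The inference in rows three and four is clear from content, but the article does not name the arm in those sentences.

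**Step 2. What two arms identify.** Write A for the effect of the application's own functions, M for the supplied monitor, training and calls, and I for any interaction. The between-arm difference estimates A + M + I. No arm receives M without A, or A without M, so one contrast cannot be divided into its parts. As an estimate of the sum it is valid.

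**Step 3. The planned effect.** The article describes 5 mmHg on a baseline of 145 mmHg as a 3.4% decrease: 5 / 145 = 3.4%, which reproduces. The 5 mmHg is also the midpoint of its source range, (4 + 6) / 2 = 5. That source concerns packages against usual care, so the assumption matches the package and not the application alone.

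**Step 4. Self-monitoring against the planned effect.** With the Introduction's range:

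- lower end: 2 / 5 = 40%
- upper end: 8 / 5 = 160%

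If effects simply add, 5 − 2 = 3 mmHg would remain for everything else at the lower end, and nothing at the upper end, since 8 exceeds 5.

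**Step 5. A figure not to use.** The Abstract's 3.2 mmHg gives 3.2 / 5 = 64%. It covers self-monitoring together with self-management, and the application is meant to deliver self-management. It therefore cannot be read as an effect that needs no application.

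**Step 6. Limits of the comparison.** No figure in the article isolates a monitor, training and calls given without an application, and the article does not say how self-monitoring was delivered in the 2 to 8 mmHg evidence. BP tracking is itself an application function. The 40% to 160% range shows that the share could be large; it does not estimate it.

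**The case against.** The strongest reply is that app plus device versus usual care is an ordinary pragmatic contrast. The title names remote monitoring and self-management. BP monitoring heads the list of application functions in Phase 2, Bluetooth integration is a stated reason for choosing Android, and the pilot is described as application plus BP apparatus. An application for tracking BP needs a cuff. The alert response is one three-level system built into the application, so it is no outside extra. The components are openly described, and the concluding statements are conditional on effectiveness. The plan also recognises that existing self-monitoring may matter: it admits people who already measure BP at least four times a week and stratifies on this, so some controls may self-monitor anyway.

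All of that stands, and it supports the package as a legitimate intervention. It does not reach the wording. Training, refreshers and calls are delivered by staff and do not come with installation, and manual entry means that the application can be used without the supplied device.

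Two stronger readings are tempting and are not supported. A reader might infer that the randomised comparison is invalid; it is valid for the package. A reader might also infer that more than half of the planned effect needs no application. That rests on the 3.2 mmHg figure, which includes self-management, and it conflicts with the 40% lower end of the self-monitoring range.

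Nor is it certain that only the intervention arm will own a supplied monitor. The limitations section offers monitors to compliant participants without naming an arm. That would not give controls training or calls.

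**Conclusion.** The concern holds as a mismatch between the contrast and the claim. The trial can estimate the effect of an app-based package (application with alert system, monitor, training with refreshers, reminder calls) against standard care. It cannot support a statement about the application alone, or about installing it. On the Introduction's figures, self-monitoring corresponds to 40% to 160% of the planned 5 mmHg, so a substantial but unknown share of any difference may not be specific to the application. This assumes that the 2 to 8 mmHg range carries over to this population, and that training and calls go to the intervention arm only, as their content indicates. The mismatch itself depends on neither the size of that share nor the planned number of participants. It should be corrected because it changes what the trial may conclude, though not how it is run.

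**What to change.** 1. Restate the objective and the intervention in the Abstract and in Phase 3 along these lines: *the effect of an app-based package (application with its alert system, supplied automated BP monitor, measurement training with monthly refreshers, and reminder calls) compared with standard care*.
2. Bring the Abstract (Results) and the Conclusion into line: limit any recommendation to the package, and remove the statement that benefit follows from installing the application.
3. Add to the limitations that the design does not isolate the application's own effect from the supplied monitor, training and staff contact.
4. State explicitly which arm receives training and calls, and reconcile the limitations section (monitors as a compliance incentive, arm not named) with Phase 3 (monitors given to the intervention group).

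The cost is editorial, and the downside is a narrower claim. No participants, visits or devices are added. Isolating the application would be a different trial, with controls given the same monitor, training and calls. If effects add and only 3 mmHg remained to be detected (Step 4), the required sample would grow by (5 / 3)² = 2.8 times, other inputs unchanged. That is not asked for here.

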**Figure 4. f4:**
[figure not shown]
Phase 3 CONSORT flow diagram.

Data will be entered and analyzed using SPSS version 22. The outcomes will be analyzed at the cluster and the individual level by intention-to-treat as well as per protocol analyses. Baseline data of all collected variables will be reported at both the individual as well as at the cluster level. The flow of participants and clusters through the various stages of the trial will be depicted through a flow diagram, giving the absolute number and reasons for non-inclusion, and non-adherence at various steps from the point of approach, recruitment, randomization, a follow-up to analysis, in both the arms. The effectiveness will be analyzed according to the principles of both intention-to-treat as well as per-protocol analysis. Multiple Imputation techniques will be employed to address missing data, with sensitivity analyses conducted to determine the impact of missing data on results and the Last Observation Carried Forward method applied for cases with intermittent missing data in follow-up measurements.

*Cluster-level analysis*

Categorical data will be summarized as proportions and quantitative data as means (or medians) and standard deviations (or interquartile range). Risk will be estimated as Relative Risk (RR). Chi-square test, repeated measures ANOVA (or Friedman’s Test) will be used to compare the 2 groups and assess the significance of any difference therein. An estimate of the effect size for the various variables will be reported along with its precision as a 2-sided 95% confidence interval. A p-value of less than 0.05 will be taken as statistically significant. Regression models will be used according to standard protocols to find out significant factors affecting the intervention at the cluster level.

*Individual-level analysis*

It will be similar to that of the cluster-level analysis except for the fact that adjustments will be made for clustering. Hierarchical regression modelling will be employed to adjust for intracluster correlation in statistical comparisons due to participants being nested within village clusters, enabling assessment of the mHealth intervention’s impact on both individual and cluster-level outcomes while accounting for potential confounders, including age, gender, baseline blood pressure, and medication adherence. In addition, the values of the intra-cluster correlation coefficient for the various outcome measures will also be reported. Subgroup analyses will be carried out and a multiplicity of analyses will be addressed.

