An open-label, parallel cluster randomised trial will be conducted from October 2023 to March 2025, with villages as the unit of randomisation into the intervention and control arm with a 1:1 allocation. Twelve villages in the Udupi district will be considered clusters in the sampling frame and eligible for randomisation. Six villages each will be allocated to either an intervention or control group, with 118 participants in each group. Randomisation will be performed by an independent biostatistics faculty using a block randomisation method (block size = 4). Allocation will be concealed using opaque, sealed envelopes to minimise selection bias. People diagnosed with hypertension within these clusters will be the targeted population. The eligibility criteria for the clusters include a hypertensive population strength ≥ 10. If a cluster fails to have the prescribed strength, it will be clubbed with an adjacent cluster to achieve the required number. For the individual participants, the eligibility criteria would be people diagnosed with primary hypertension and on medical management (ICD 10 code: I10) for the last 5 years, of either gender, between the ages of 18 and 60 years, who will be able to comprehend health messages in English or Kannada and have access to Android-based smartphones with internet connectivity. The Android platform requirement aligns with the prevalent smartphone ecosystem in the region, where Android devices account for over 90% of the market share among our target demographic, ensuring maximum study feasibility and real-world applicability. We will be excluding people undergoing any other structured behaviour change intervention who are dependent on self-care. Participants currently engaged in regular self-monitoring of blood pressure (defined as measuring BP ≥4 times per week for the past 3 months) will be eligible for inclusion. Still, they will be stratified during randomisation to ensure balanced distribution across intervention and control groups. This approach acknowledges that existing self-monitoring behaviour may influence intervention effectiveness while maintaining the study’s external validity.

The sample size was calculated based on the primary outcome of mean systolic blood pressure reduction, using the formula for cluster randomised trials:

$$n=\left[{\left(z_{\alpha /2}+z_{1-\beta }\right)}^{2},\left\{\left(\sigma_{1}^{2}+\sigma_{2}^{2}\right),/,\delta^{2}\right\}\right]\left[1+\left(m-1\right)\rho \right]$$

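### In the cluster-level analysis, Friedman's test cannot compare the two arms, and a chi-square test on participant counts ignores village clustering

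*Protocol article*

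**What the plan says.** The protocol article (Methods, Phase 3) randomises villages: "the villages would be the units of randomization". On size it states: "Six villages each will be allocated to either an intervention or control group, with 118 participants in each group".

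The analysis text plans two levels: "The outcomes will be analyzed at the cluster and the individual level by intention-to-treat as well as per protocol analyses". Under Cluster-level analysis, categorical data become proportions, risk is expressed as a relative risk, significance is set at p < 0.05, and the tests are these: "Chi-square test, repeated measures ANOVA (or Friedman’s Test) will be used to compare the 2 groups".

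Under Individual-level analysis the article says: "It will be similar to that of the cluster-level analysis except for the fact that adjustments will be made for clustering". It continues: "Hierarchical regression modelling will be employed to adjust for intracluster correlation in statistical comparisons", with participants nested in villages and intra-cluster correlations to be reported.

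The sample size paragraph supplies the clustering inputs: "With 90% power, 5% significance level (two-sided), design effect of 1.45 (ICC = 0.05), and accounting for 15% attrition", with clusters of about 20.

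**The concern.** The article names these tests and gives their purpose, which is to compare the two arms. That is a stated choice, so neither the condensed format nor an analysis plan that is not shown explains it.

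Friedman's test answers a different question: whether measurements differ between occasions within the same blocks. Control participants also receive advice on adherence and an active lifestyle, so blood pressure could fall in both arms. A significant Friedman result could then be read as evidence that the application works.

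For chi-square, proportions and relative risks point to participant counts. The individual-level section presents the clustering adjustment as what distinguishes it from the cluster-level section. On that reading the chi-square test carries no adjustment, and it would reject a true null hypothesis too often.

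**Working it through.** **1. The plan's own clustering figure.** The article's formula gives design effect = 1 + (m − 1)ρ.
- With ρ = 0.05 and m = 20: 1 + 19 × 0.05 = 1.95.
- The stated 1.45 is what m = 10 gives: 1 + 9 × 0.05 = 1.45.

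The stated value therefore does not follow from about 20 per village. That is a separate matter, and both values are carried forward here.

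**2. Chi-square on participant counts, by formula.** Under the null hypothesis the unadjusted statistic, on the z scale, has variance equal to the design effect (DE) and not 1. The true two-sided type I error is 2[1 − Φ(1.96/√DE)].
- DE = 1.45: 1.96/1.204 = 1.628, giving 0.104.
- DE = 1.95: 1.96/1.396 = 1.404, giving 0.160.

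**3. Chi-square, by simulation.** Beta-binomial data, 6 villages per arm, 20 per village, 20,000 runs, outcome proportions 0.1, 0.3 and 0.5:

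| ICC of the binary outcome | Chi-square on participants | t-test on village proportions |
|---|---|---|
| 0.05 | 15.5-16.0% | 4.7-4.9% |
| 0.02 | 8.6-9.7% | 4.8-5.1% |
| 0.01 | 6.5-7.4% | 4.8-5.1% |

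The ICCs of 0.01 and 0.02 are assumptions. The article gives an ICC only for its sample size, which is based on systolic pressure.

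If ICC 0.05 holds for systolic pressure and that outcome is dichotomised, the binary ICC is lower. For a cut at the median it is (2/π) × arcsin(0.05) = 0.032. Then DE = 1 + 19 × 0.032 = 1.61 and the formula gives 2[1 − Φ(1.96/1.268)] = 0.122. Simulation of this case (12 villages of 20) gave 11.6%. Hence the range of 12-16% at ICC 0.05.

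**4. Chi-square on villages.** The test needs counts, and 12 village proportions are not counts. If each village were classed as high or low instead, the expected count per cell would be at most 6 × 6/12 = 3, too few for the chi-square approximation.

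**5. Friedman's test, by algebra.** With b blocks and k occasions, Q = 12/[bk(k + 1)] × ΣR_j² − 3b(k + 1), where R_j is the sum over blocks of the within-block ranks at occasion j. Arm appears nowhere. Adding any constant to every value in one arm leaves all ranks, and so Q, unchanged.

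**6. Friedman's test, by simulation.** Blocks are 12 villages. Three occasions and village-level SDs of about 3.3 mmHg (between villages and within village over time) are assumptions. There were 2,000 runs per row.

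| True situation | Friedman p < 0.05 |
|---|---|
| No effect, no trend | 5.6% |
| No effect, both arms fall 5 mmHg | 77.5% |
| Constant arm difference of 5 mmHg, no trend | 6.0% |
| Constant arm difference of 20 mmHg, no trend | 6.3% |

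In the second row a t-test on village changes rejected in 4.3%, close to its nominal 5%.

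With 236 participants as blocks (three visits and within-person correlation 0.6, both assumed), a shared 3 mmHg fall with no effect was significant in 73-75% of runs, and a shared 5 mmHg fall in over 99%. With the arms moving in opposite directions to a true 5 mmHg difference at the last visit, it was significant in only 4.9%.

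**The case against.** - **Repeated measures ANOVA is sound.** It is named ahead of Friedman's test, which stands only in brackets as the alternative. On village means with arm as a between-village factor, its arm-by-time term is a valid comparison. This stands. A reader might infer that every between-group test in the section is invalid, and the document does not support that.
- **The unit is ambiguous.** The section is headed cluster-level, the article never says that adjustment is made only at the individual level, and village summaries need no further adjustment. This stands in part: inflation from clustering follows only if chi-square is run on participants. That is the natural reading of proportions with a relative risk, but it is a reading. The village reading does not save the test (step 4).
- **The trial does account for clustering.** The individual-level hierarchical model does so. A reader might infer that the trial ignores clustering altogether, and that would be wrong.
- **The sizes are not all the protocol's.** The article fixes no three-visit schedule; for the questionnaires it mentions a pre-test and a post-test. It gives no ICC for any binary outcome. Quoting 16% alone would overstate the case. The missing arm term in Friedman's test depends on none of these assumptions.
- **Chi-square does not bear on mean systolic pressure**, which is continuous and is the outcome used for the sample size. This stands and limits the consequence to categorical outcomes.
- **No single primary analysis is named.** That is commonly left to an analysis plan and is not counted as a fault here.

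**Conclusion.** The point holds for two of the three named tests. Friedman's test cannot compare the arms under any reading. Its response to a shared trend is large (77.5% for a 5 mmHg fall on village data), but that size rests on the assumed occasions and variances.

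The chi-square test, read as a test on participant counts, has a true type I error of about 10% at the stated design effect and about 12-16% with ICC 0.05 and 20 per village. The figure is about 6.5-10% if the binary-outcome ICC is 0.01-0.02. Read as a test on villages, it does not suit the data.

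The plan has sound routes to a comparison in repeated measures ANOVA on village means and in the hierarchical model. The text should therefore be corrected, but the fault does not undermine the trial. Nothing here depends on whether 118 per arm is the right sample size.

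**What to change.** In the Cluster-level analysis section:
- Delete Friedman's test and the unadjusted chi-square test as between-arm tests.
- State that the unit is the village summary: mean change in systolic pressure, or the proportion for a categorical outcome.
- Compare 6 with 6 villages by a two-sample t-test on 6 + 6 − 2 = 10 degrees of freedom, or by a rank or permutation test. A permutation test must follow the allocation scheme actually used, because the article allows villages to be merged and mentions stratification.
- If repeated measures ANOVA is kept, say that it is run on village means and that the arm-by-time term is tested.

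Base conclusions on the clustering-adjusted hierarchical model already planned for the individual level, with the village-summary analysis as supportive.

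The cost is a few sentences and a little analysis work. No change to data collection is needed.

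### The village-level repeated measures ANOVA leaves open which term is tested and what role baseline plays; a baseline-adjusted comparison would be as strong or stronger

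*Protocol article*

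**What the plan says.** In the sample size paragraph of Phase 3, the Protocol article states: "The sample size was calculated based on the primary outcome of mean systolic blood pressure reduction". Measurement before the intervention is planned in both arms: "Baseline measurements like blood pressure, knowledge and practice of management of blood pressure, self-efficacy, and health status will be obtained".

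For the comparison of arms, Cluster-level analysis states that "repeated measures ANOVA (or Friedman’s Test) will be used to compare the 2 groups and assess the significance of any difference therein". An effect size with a two-sided 95% confidence interval is to be reported as well. The section does not name the group main effect, the group-by-time term or a baseline-adjusted comparison. It does not say whether baseline is one of the repeated levels.

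Individual-level analysis opens with: "It will be similar to that of the cluster-level analysis except for the fact that adjustments will be made for clustering". It then adds a hierarchical regression with baseline blood pressure among the factors accounted for. Neither analysis is named as primary. The number of blood pressure occasions entering the ANOVA is not given. A pre-test and post-test are mentioned for the questionnaires, while the missing-data text speaks of intermittent gaps in follow-up, which suggests more than one follow-up.

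**The concern.** A two-group repeated measures ANOVA produces two lines that could be read as comparing the groups. The between-subjects group effect averages over all occasions. If baseline is one of them, a value taken before treatment is averaged into the estimate and shrinks it. The group-by-time term compares the arms on change, which is what a reduction means. The stated purpose is only to compare the two groups, and that fits the wrong line at least as easily as the right one.

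The two lines differ in estimate and in power, and the plan does not say which decides. The trial is open-label and has 12 villages, so a choice made after seeing the data would be hard to defend. Chance differences at baseline between six and six villages are to be expected, and the candidate tests respond to them differently.

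This point concerns the repeated measures ANOVA only, not Friedman's test or the chi-square test.

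**Working it through.** **The plan's own figure.** The inputs are: "we anticipate a conservative effect size of 5 mmHg reduction in systolic BP"; "Assuming a baseline systolic BP of 145 ± 15 mmHg in our population"; "With 90% power, 5% significance level (two-sided), design effect of 1.45 (ICC = 0.05), and accounting for 15% attrition". The article's formula gives (1.960 + 1.282)² × (2 × 15²)/5² = 189.1. Multiplied by 1.45 this is 274.2 per arm, and divided by 0.85 it is 322.6. The stated 118 per arm is not reproduced. That is a separate matter, but it means the planned 90% cannot serve as the benchmark here. The tests below are compared at the size to be enrolled.

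**Inputs for the comparison.** Taken from the article: 6 v 6 villages, about 20 per village less 15% (17 analysed), SD 15, ICC 0.05, effect 5 mmHg, two-sided 5%. Assumed: one baseline and one follow-up, and a correlation r between village baseline and follow-up means of 0.4 to 0.8. The article gives neither.

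**Variance of a village mean.** v = 225 × (0.05 + 0.95/17) = 23.8. This uses the stated ICC directly, not the stated design effect.

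**Worked case, r = 0.6**
- Group main effect: the effect is 5/2 = 2.5. The variance is v(1 + r)/2 = 19.1, so SE = √(2 × 19.1/6) = 2.52 and the ratio is 0.99.
- Group-by-time (identical to change from baseline): the effect is 5. The variance is 2v(1 − r) = 19.1, so SE = 2.52 and the ratio is 1.98.
- Follow-up only: the effect is 5, SE = √(2 × 23.8/6) = 2.82 and the ratio is 1.77.
- ANCOVA: the effect is 5. The variance is about v(1 − r²) = 15.2, so SE = 2.25 and the ratio is 2.22.

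**Simulated power at village level** (t tests on 10 df, ANCOVA on 9 df; repeat runs agree to about one point)

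| Test | r = 0.4 | r = 0.6 | r = 0.8 |
|---|---|---|---|
| Group main effect, baseline included | 16% | 15% | 13% |
| Group-by-time | 31% | 43% | 72% |
| Follow-up only | 36% | 36% | 36% |
| ANCOVA on baseline | 38% | 47% | 71% |

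**More follow-ups.** With k follow-ups and a constant effect, the group term keeps k/(k + 1) of the effect: 50%, 67% and 75% for k = 1, 2 and 3. At r = 0.6 its power with two or three follow-ups is about 24% or 30%, against 62% or 69% for ANCOVA.

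**Type I error.** Over all trials with no treatment effect it is about 5% for every test. In trials where the arms differ at baseline by at least one SE, it is about 14 to 16% for the group main effect and roughly 8 to 10% for group-by-time at r = 0.4 to 0.6 (about 6% at r = 0.8). For ANCOVA it is about 5%.

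**The case against.** The strongest reply is that the article never chooses the group main effect. The same ANOVA yields group-by-time. With one baseline and one follow-up, that is exactly the test of a difference in mean reduction, and since the outcome is defined as a reduction it is the more natural reading. Nor does the article say that baseline is a repeated level; if only follow-ups are, nothing is diluted. The choice of term could be left to a fuller document. The hierarchical model already accounts for baseline pressure and is said to address cluster-level outcomes too. Finally, low power at village level comes mainly from having 12 villages: even ANCOVA stays below 50% up to r = 0.6.

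Much of this stands. A reader might infer that the plan tests the diluted main effect, that it therefore tests a different null hypothesis, and that it halves the effect and loses most of the power. The article does not support that. The main effect is only the least favourable reading. Under randomisation its expectation is zero exactly when the treatment effect is zero. Halving needs exactly one follow-up, and the power loss depends on an unstated correlation: at r = 0 the main effect loses nothing against group-by-time. Nor does any text say that the individual-level model keeps baseline in the outcome.

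The reply does not remove the point. The article does name a method for this comparison, and over r = 0.4 to 0.8 baseline-adjusted ANCOVA matches or beats each way of reading it, using a value that is already collected. The hierarchical model stands under the individual-level analysis and is not named as primary.

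**Conclusion.** The point holds as a badly fixed test with a better alternative at hand, not as a plan that is shown to use a wrong test. If the group main effect is used with baseline included and one follow-up, power for 5 mmHg is about 13 to 16%, against 38 to 71% for ANCOVA, and the reported effect is half the true one. If group-by-time is used, the test is valid. It gives up about 7 points to ANCOVA at r = 0.4 and 4 points at r = 0.6, with no material difference at r = 0.8, and it keeps some exposure to chance baseline imbalance. If only follow-up is analysed, power is about 36% whatever the correlation.

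These figures rest on 17 analysed per village, SD 15, ICC 0.05 and the assumed correlation range. Below that range ANCOVA's advantage over follow-up alone disappears: at r = 0.2 it has about 35%, against about 36%.

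**What to change.** In Cluster-level analysis, replace repeated measures ANOVA as the between-arm test with wording such as: Village mean follow-up systolic blood pressure will be compared between arms by ANCOVA with the village mean baseline value as covariate (9 degrees of freedom); the adjusted difference and its 95% confidence interval are the effect estimate. The same form suits the other continuous outcomes.

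If repeated measures ANOVA is kept, state that the group-by-time contrast, not the group main effect, is the test of effectiveness, and say which occasions enter the model.

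In Individual-level analysis, keep baseline pressure as a covariate and state that it is not also part of the outcome.

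The cost is wording plus one degree of freedom (10 to 9), which the ANCOVA power figures already include. No new data are needed.
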